### Implementation and sustainment facilitation strategy

Encompassed within the overarching strategy of using an implementation advisor are six additional discrete strategies. Supplementing the specifications in Table 3, descriptions of each of these strategies are provided here.(K)
Use an improvement/implementation advisor Consistent with prior research [38, 66–69], use of an implementation advisor was operationalized as an individual external to the organization who utilized interactive problem-solving and support to help the organization identify and achieve improvement and implementation goals.(L)
Develop tools for quality improvement Five quality improvement tools were developed and are described below.

First, the past implementation effort exercise, based on research emphasizing the importance of using past performance to improve future practice [70], was developed to facilitate organizations sharing with their advisor a past experience implementing an innovation. In addition to describing the past effort, organizations discussed the extent to which the effort was ultimately successful, unsuccessful, or had mixed results. Advisors used reflective listening skills to highlight the importance of the organization’s past implementation effort and how learning from the past may help them successfully achieve the goals of the current project’s preparation, implementation, and sustainment phases.

Next, the decisional-balance exercise was developed based on supporting research [71] and sought to evoke reasons behind the organization’s decision to implement the MIBI for substance use and to identify potential barriers.

Third, the ISF Workbook (a Microsoft Excel-based electronic workbook) was developed to standardize ISF strategy implementation, the lack of standardization having been a criticism of many implementation studies [41]. The ISF Workbook has five worksheets: (1) a project charter worksheet that lists the project’s goals, staff working on the project (SWOP) team members, and the implementation advisor’s name and contact info; (2) a meeting attendees and notes worksheet with a placeholder for documenting the date of all expected ISF meetings, the SWOP team members that attended each meeting, summary notes from the meeting, and a link to the meeting recording; (3) a preparation phase worksheet that includes the goals of the preparation phase and the ISF strategy’s performance review, evaluation, and planning exercise; (4) an implementation phase worksheet that includes the goals of the implementation phase and the ISF strategy’s performance review, evaluation, and planning exercise; and (5) a sustainment phase worksheet that includes a placeholder for entering what (if anything) the organization chooses as their goal(s) for the sustainment phase and the ISF strategy’s performance review, evaluation, and planning exercise.

Next, the process walk through exercise was developed based on prior research that has found walking through the steps of a process to be a helpful quality improvement tool [38, 72]. The process walk through exercise was conducted by having the SWOP team review a detailed process flow diagram with the following four key questions emphasized throughout the exercise: What is working well? What needs improvement? What is the plan for improving what needs improvement? What is the plan for maintaining what is working well? Although time was spent on what was working well and the plans for maintaining what was working well, explicit emphasis was on identifying what needs improvement and plans to enact improvements.

Last, the implementation climate evaluation exercise was developed to standardize an advisor’s process of evaluating the implementation climate for the MIBI (i.e., the extent to which it is expected and supported). Implementation climate has been hypothesized as a key mechanism of change for implementation strategies’ impact on implementation effectiveness [31–33, 73]. When there was no consensus on the implementation climate or when the implementation climate was poor, the ISF advisor sought to evoke reasons for the current beliefs, find ways to better align staff members’ beliefs, and develop plans to optimize the implementation climate. In contrast, when there was consensus on the implementation climate or when the implementation climate was strong, advisors facilitated discussion around maintaining or improving it.(M)
Organize implementation team meetings Organizing implementation team meetings that SWOP team members were willing and able to regularly attend was one of the most important strategies [74, 75]. ISF advisors sought to organize recurring implementation team meetings early in the process. Monthly team meetings were conducted via join.me, a collaboration tool with advanced phone conference and screening sharing capabilities. In addition, a limited number of in-person team meetings (typically just one) were organized for a day during the second month of the implementation phase.(N)
Identify and prepare champions Consistent with research highlighting the importance of having someone championing the organization’s implementation efforts [31, 32, 76, 77], an ISF advisor’s focus on champion identification began immediately upon formal introduction to the organization and its SWOP team. The ISF advisor paid attention to the extent SWOP team members responded to emails and meeting discussions as a way of identifying team members’ levels of engagement and team influence. Once an ISF advisor identified a potential champion, they sought to optimize the individual’s commitment to the project and its goals.(O)
Assess for readiness and identify barriers Building on extant research on readiness assessment and barrier identification [78–82], the ISF strategy included exercises developed to assist with assessing readiness and identifying barriers (e.g., past implementation effort exercise, decisional balance exercise, process walk through exercise), which were described earlier (see Develop tools for quality improvement).(P)
Conduct local consensus discussions Consensus-building is an important strategy [83, 84]. Thus, concerted efforts were directed towards conducting local consensus discussions with key stakeholders, who are internal or external individuals that the SWOP team considered key to directly and/or indirectly helping sustain the MIBI services over time. Key stakeholders were invited to attend the in-person ISF meeting to learn about the project and participate in a formal sustainment planning discussion.(Q)
Conduct cyclical small tests of change Cyclical small tests of change, such as plan-do-study-act cycles are a valuable quality improvement strategy [85–87]. Within the ISF strategy, however, this cycle was reframed into a study-act-plan-do cycle. This reframing was done to emphasize the importance of beginning with the study phase by assessing existing performance and then deciding about the need to act (or not act). When action or change was deemed necessary, a plan was developed and then implemented in the do phase.

### Outcomes

Table 7 describes the three staff-level outcome measures (i.e., time-to-proficiency, implementation effectiveness, and level of sustainment) used to examine the extent to which the ISF strategy serves as an effective adjunct to the ATTC strategy. Additionally, Table 7 describes the two staff-level measures (i.e., personal recovery status and motivational interviewing experience) and four organizational-level measures (i.e., readiness for implementing change, implementation climate, leadership engagement, and tension for change) that have been hypothesized as moderators of the relationship between organizational condition assignment (ATTC vs. ATTC + ISF) and each respective primary outcome measure.

**Table 7 Tab7:** Instruments, instrument-related procedures, and measures

Measurement instrument	Measurement instrument time points and procedures					
	Staff survey #1 (t = month 0)	Preparation phase assessment (t = months 1–6)	Implementation phase assessment (t = months 7–12)	Staff survey #2 (t = month 13)	Staff survey #3 (t = month 19)	Measure name (purpose) Description
Independent Tape Rater Scale [26]		X^a^				Time to proficiency (preparation outcome) A continuous staff measure representing the number of days between completion of the workshop training by BI staff and their demonstration of proficiency [26, 30] in the motivational interviewing-based brief intervention (MIBI)
Independent Tape Rater Scale [26]			X^b^			Implementation effectiveness [31] (implementation outcome) A continuous staff measure representing the sum of the standardized cumulative number of MIBIs delivered by BI staff (i.e., consistency) and the cumulative integrity score of their delivery of the MIBI (i.e., quality)
Staff survey	X^c^			X^c^	X^c^	Level of sustainment (sustainment outcome) A continuous staff measure (no specified range) that represents the number of MIBIs a BI staff self-reports having delivered during the past 6 months
Staff survey	X^c^			X^c^	X^c^	Motivational Interviewing Experience (moderator variable) A staff measure indicating a BI staff’s perception of their motivational interviewing experience (0 = none, 1 = beginner, 2 = intermediate, 3 = advanced, 4 = expert)
Staff survey	X^c^			X^c^	X^c^	Readiness for implementing change (moderator variable) A continuous organization measure (ranges from 1 to 5) that represents the organizational average of 6 items, each rated on a 5-point scale (1 = disagree, 2 = somewhat disagree, 3 = neither agree nor disagree, 4 = somewhat agree, 5 = agree) and adapted from Shea et al.’ readiness measure [106]
Staff survey	X^c^			X^c^	X^c^	Implementation climate (moderator variable) A continuous organization measure (ranges from 1 to 5) that represents the organizational average of 6 items, each rated on a 5-point scale (1 = disagree, 2 = somewhat disagree, 3 = neither agree nor disagree, 4 = somewhat agree, 5 = agree) and adapted from Jacobs et al.’ implementation measure [107]
Staff survey	X^c^			X^c^	X^c^	Leadership engagement (moderator variable) A continuous organization measure (ranges from 0 to 6) that represents the organizational average of 4 items, each rated on a 7-point scale (0 = not at all to 6 = highest extent possible) and developed for this study based on the leadership engagement construct described by Damschroder et al.—commitment, involvement, and accountability of leaders with the implementation [108]
Staff Survey	X^c^			X^c^	X^c^	Tension for change (moderator variable) A continuous organization measure (ranges from 0 to 6) that represents the organizational average of 3 items, each rated on a 7-point scale (0 = not at all to 6 = highest extent possible) and developed for this study based on the tension for change construct described by Damscroder et al.—stakeholders’ shared perception of the extent to which a change is important, needed, and desired [108]

^a^Ratings during the preparation phase were completed by one of the co-authors (DV)

^b^Ratings during the implementation phase were rated by one of 15 experienced raters, each of which were trained, calibrated, and monitored by one of the co-authors (SM)

^c^Staff surveys (electronically administered) required approximately 30 min to complete, and staff received one $25 e-gift card per completed survey as compensation

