### The ISF Experiment’s Objective and Scientific Hypotheses

Testing the effectiveness of the ISF strategy as an adjunct to the ATTC strategy is the ISF Experiment’s key objective. Table 1 lists the planned scientific hypotheses for the ISF Experiment, which were guided by use of a decomposed-first strategy [39] that advocates for starting with moderation-focused hypotheses to avoid biases associated with conflated effects.

**Table 1 Tab1:** Planned scientific hypotheses

Hypotheses	
H1	The positive relationship between the implementation and sustainment facilitation and staff time-to-proficiency will be moderated by
	H1a Staff’s motivational interviewing experience
	H1b Staff’s personal recovery status
	H1c Organization’s readiness for implementing change
	H1d Organization’s implementation climate
	H1e Organization’s leadership engagement
	H1f Organization’s tension for change
H2	The positive relationship between the implementation and sustainment facilitation and staff implementation effectiveness will be moderated by
	H2a Staff’s motivational interviewing experience
	H2b Staff’s personal recovery status
	H2c Organization’s readiness for implementing change
	H2d Organization’s implementation climate
	H2e Organization’s leadership engagement
	H2f Organization’s tension for change
H3	The positive relationship between the implementation and sustainment facilitation and staff level of sustainment will be moderated by
	H3a Staff’s motivational interviewing experience
	H3b Staff’s personal recovery status
	H3c Organization’s readiness for implementing change
	H3d Organization’s implementation climate
	H3e Organization’s leadership engagement
	H3f Organization’s tension for change
H4	Staff implementation effectiveness will mediate the relationship between staff time-to-proficiency and staff level of sustainment

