Distribute educational materials Consistent with research supporting the importance of using multiple dissemination strategies [45, 46, 54], the educational materials were distributed to BI staff. BI staff were emailed links to the online educational course [47] and printed copies of the MIBI protocol manual [48] were hand-delivered to staff at the in-person workshop training.(F)
Conduct educational meetings Research has not found educational materials by themselves to be sufficient for learning motivational interviewing [30, 55]. Thus, Web-based and in-person educational meetings were also provided, including a two-day in-person workshop training for BI staff on the MIBI protocol.(G)
Make training dynamic Role plays that enable trainees to practice with other trainees and facilitate understanding of the EBP from both the staff and client perspectives have been found to make motivational interviewing training more dynamic [30, 55, 56]. In addition to using role plays multiple times during the in-person workshop training, trainees were given role plays to complete during the week after the workshop training.(H)
Audit and provide feedback There is support for audit and feedback as an effective strategy, both in general [57–60] and specifically with learning motivational interviewing [30]. Thus, standardized feedback reports based on ratings using the validated Independent Tape Rater Scale [26] were provided to BI staff for all sessions completed and recorded.(I)
Provide ongoing consultation Providing ongoing consultation following workshop training has been supported as an important strategy to facilitate learning of psychosocial interventions [30, 36, 61]. During the 10-week post-workshop-training practice period, each trainee was allowed up to four individual consultation sessions with a member of the Motivational Interviewing Network of Trainers (MINT) [62].(J)
Create a learning collaborative The use of a learning collaborative has been identified as an important method of learning [63–65]. Thus, each month during the 6-month implementation phase, a motivational interviewing expert from MINT [62] organized and moderated two 1-h learning collaborative meetings, one for the ATTC only condition and one for the ATTC plus ISF condition.

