### Data collection, management, and analysis

#### Data collection and management

The Independent Tape Rater Scale (ITRS) was used to assess proficiency in motivational interviewing and implementation effectiveness. The ITRS is a well-validated tool for assessing two key factors: adherence and competence [26]. Confirmatory factor analysis has supported the two-factor structure of the ITRS [26], and excellent levels of inter-rater reliability have been found for both motivational interviewing adherence (mean ICC .89; range .66–.99) and competence (mean ICC .85; range .69–.97) [26].

The lead developer of the MIBI protocol (co-author SM) oversaw the selection, training, calibration, and supervision of the project’s 15 MIBI raters, who were blinded to study condition. Booster trainings and recalibration of the raters were conducted in between cohorts. Consistent with the established guidelines promoted in the motivational interviewing assessment: Supervisory Tools for Enhancing Proficiency [93], BI staff were considered to have demonstrated proficiency when at least half of the 10 motivational interviewing consistent items were rated 4 or greater on a 7-point scale for both adherence and competence. Submissions of MIBI sessions from BI staff and ratings from MIBI raters were enabled via a secure, Web-based implementation tracking system adapted from one used in our prior implementation research [94]. In addition to enabling MIBI raters to stream the audio files rather than download, an important security feature, the Web-based system allowed MIBI raters to enter adherence and competence ratings directly into the secure and backed-up database located on RTI’s servers.

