### Statistical methods

Statistical analyses will be conducted using an intention-to-treat analysis approach, which will analyze all ASOs as randomized. Hot-deck imputation [95, 96] will be used to address missing data issues, which are anticipated to be minimal (i.e., less than 5%). Analyses will be conducted using HLM software [97], which is well-suited for handling clustered data (i.e., time nested within staff, nested within organization). Analyses will be conducted in the order outlined in Table 1. In addition to reporting the coefficient, standard error, 95% confidence interval, and *p* value, results will also include effect size indicators.

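### Time-to-proficiency has no stated value for staff who do not reach proficiency in the preparation phase, and hot-deck imputation, the only rule for absent values, would bias the ISF effect toward zero if applied to them

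*Protocol article*

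**What the plan says.** The Rationale for the primary outcomes names days-to-proficiency as the primary preparation outcome. Table 7 (Outcomes) defines it as "A continuous staff measure representing the number of days between completion of the workshop training by BI staff and their demonstration of proficiency" and places its assessment in the preparation phase, months 1–6.

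Data collection and management sets the criterion: "BI staff were considered to have demonstrated proficiency when at least half of the 10 motivational interviewing consistent items were rated 4 or greater". Adherence and competence must each satisfy this rule, and ratings use seven points.

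Table 4 puts the 16 hours of training in month 4 of the six-month phase. The description of ongoing consultation in the ATTC strategy section refers to ten weeks of practice afterwards: "During the 10-week post-workshop-training practice period, each trainee was allowed up to four individual consultation sessions".

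Statistical methods has three relevant sentences. On population: "Statistical analyses will be conducted using an intention-to-treat analysis approach, which will analyze all ASOs as randomized". On absent values: "Hot-deck imputation [95, 96] will be used to address missing data issues, which are anticipated to be minimal (i.e., less than 5" per cent. On the model: "Analyses will be conducted using HLM software [97], which is well-suited for handling clustered data".

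Table 1 words H1 as "The positive relationship between the implementation and sustainment facilitation and staff time-to-proficiency will be moderated by" six staff and organization factors. H4 uses time-to-proficiency as its predictor.

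**The concern.** A threshold that must be met in a finite period can be missed. For a staff member whose recordings were rated and never met it, the data say only that the time exceeds the observation window. That is a right-censored observation, but Table 7 describes a plain continuous count of days, which such a person does not have.

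If these blanks are treated as missing data, the stated remedy is hot-deck. Every possible donor reached proficiency, so each filled value lies within the range of the successes. The worst result on this outcome, and the one ISF is meant to make rarer, would be recorded as an ordinary success. With two BI staff per ASO, one filled value is half of that ASO's data. H4 would inherit the same values.

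A smaller matter is direction. H1 to H3 share one sentence pattern. For implementation effectiveness and level of sustainment, higher is better, so a positive relationship is a benefit. On a scale of days it literally means slower.

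**Working it through.** **1. The plan's own figure.** Sample size states 80% power at effect size .67 with 39 ASOs, 2 staff each and ICC .05. With the two-level formula, λ = J·d² / {4[ρ + (1 − ρ)/m]} = 39 × 0.4489 / {4 × [0.05 + 0.475]} = 17.507 / 2.1 = 8.34. Noncentral F on 1 and 37 degrees of freedom gives power 0.803. The figure reproduces, but for an outcome observed on all 78 staff.

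**2. Assumptions for the check.** The documents give no attainment rate and no window end. I assume exponential times, W = 70 days (the ten practice weeks), 20 ISF and 19 control ASOs, and attainment p by day 70 as shown. With s = W / [−ln(1 − p)]:
- restricted mean (non-attainers held at 70 days) = p·s
- mean among attainers = s − W(1 − p)/p, which is also the expected arm mean after hot-deck from donors in the same arm
- pooled hot-deck arm mean = p × (attainers' mean) + (1 − p) × (mean of all donors)

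**3. One case in full: 95% control, 98% ISF.** Control: s = 70/2.996 = 23.37, restricted mean 22.20, attainers' mean 23.37 − 3.68 = 19.68. ISF: s = 70/3.912 = 17.89, restricted mean 17.54, attainers' mean 17.89 − 1.43 = 16.46. The difference is −4.66 days restricted and −3.22 with within-arm donors. The pooled donor mean is 18.01, giving arm means 19.60 and 16.50 and a difference of −3.10. The expected number of non-attainers is 38 × 0.05 + 40 × 0.02 = 2.7 of 78.

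**4. Range.** ISF minus control, in days:

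| Proficient by day 70, control / ISF | Restricted days | Within-arm donors (lost) | Pooled donors (lost) |
|---|---|---|---|
| 95% / 98% | −4.66 | −3.22 (31%) | −3.10 (33%) |
| 80% / 90% | −7.43 | −3.37 (55%) | −2.85 (62%) |
| 70% / 90% | −13.34 | −5.52 (59%) | −4.33 (68%) |
| 60% / 80% | −11.04 | −3.73 (66%) | −2.55 (77%) |
| 50% / 75% | −12.62 | −3.83 (70%) | −2.28 (82%) |

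**5. Power.** Simulation with within-ASO correlation .05 and a t-test on ASO means (2,000 trials per case) gives differences close to these. Power for restricted days, then within-arm, then pooled donors:
- 95/98%: .19, .14, .13
- 80/90%: .26, .16, .09
- 60/80%: .46, .21, .10
- 50/75%: .56, .23, .08

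Weibull times with shape 1.5 give similar power.

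**6. Type I error.** With no true effect and an ASO frailty SD of 0.3, within-arm donors give about 6% when 97% are proficient, 6–7% at 95%, 8% at 90%, 13–14% at 70% and 20–22% at 50%. Invented values are counted as independent data, and each arm's fills repeat that arm's chance deviation. Pooled donors stay near 5%.

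**The case against.** The strongest reply is that the article nowhere says non-attainers will be hot-decked. Someone who was rated and fell short has observed ratings, so the result need not count as missing. The article names software, not a model for each outcome. Table 7 also calls a count of delivered interventions continuous, so the word may be a loose label. A censoring rule could sit in a full protocol or analysis plan that is not shown.

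Much of this stands. A reader might infer that the plan commits to hot-decking these staff, but that follows only from its being the sole stated rule. Even so, the definition itself leaves them without a value. If they are neither imputed nor censored they drop out, and the expected difference is then the attainers' difference, the same as in the within-arm column. Dropping them also fits poorly with analysing everyone as randomized.

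Three further readings are tempting and not supported:
- *Observation stops at day 70.* The ten weeks describe when consultation was available; Table 7 says only the preparation phase. Seventy days is my assumption.
- *Most of a real effect is lost.* That needs non-attainment well above the under-5% missing data that the article expects. If that figure is meant to include non-attainers, the loss is about a third of the difference and 5 to 6 points of power.
- *H1 is reversed, so slower proficiency under ISF would support it.* The shared template shows that benefit is meant, no one-sided test is stated, and a two-sided test is unchanged.

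**Conclusion.** The point holds in a limited form. The article fixes a primary outcome as days to a threshold that can be missed, gives no value to those who miss it, and offers only a rule for absent values that would record a failure as a success. If that rule is applied and ISF does raise attainment, the estimated benefit moves toward zero.

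The size is conditional on the unknown attainment rate, exponential times and a 70-day window. About 1.5 of 4.7 days is lost when 2–5% fail, and 62% to 82% of the difference with pooled donors when 10–50% fail. Within-arm donors lose somewhat less but inflate the type I error, slightly at low non-attainment and severely at high. If every staff member becomes proficient there is no distortion. The direction of bias is firm; its size in this trial cannot be known from the document. The H1 wording is an editorial inconsistency with Table 7 and changes no result.

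**What to change.** State a fixed end of the observation window for time-to-proficiency. Treat staff who were rated but not proficient by then as right-censored at that point. Analyse with a clustered time-to-event model, for example a discrete-time hazard model with an ASO random intercept. Restricted days, with non-attainers set to the window end and ASO as a random effect, would also serve. Reserve hot-deck for ratings that are truly missing, such as a lost or unrated recording, and report non-attainers by arm separately from missing data. Carry the same definition into H4, for example as restricted days plus an indicator of proficiency. Reword H1 to say that ISF shortens days to proficiency.

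This changes analysis wording only and needs no new data. The cost is that the effect becomes a hazard ratio or a restricted-mean difference rather than a standardized mean difference, so it no longer maps directly onto the .67 in Sample size.
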